#### Predetermined visit schedule

The visit schedule for all assessments is presented in Table 1. Participants will be evaluated at screening (Week −2), baseline (Week 0), post-treatment (Week 4), and follow-up (Weeks 6, 8, 16, and 28). Demographic characteristics and medical history will be collected only at the first visit. Baseline assessments, including CRS-R, fNIRS, EEG, ERPs, GOS-E, and fMRI, will be conducted at Week 0, followed by randomization and treatment initiation. The primary outcome measure (CRS-R) will be assessed at all visits starting from baseline. Secondary outcome measures will be measured at various time points. All follow-up visits will be conducted in outpatient settings. For patients unable to attend in person, home visits or video follow-ups will be arranged (22).

**Table 1 tab1:** Schedule of enrolment, interventions, and assessments.

	Study Period						
	Screening	Baseline	Treatment	Follow-up			
Week	−2	0	4	6	8	16	28
Enrolment							
Eligibility screen	**×**						
Signed informed consent	**×**						
Allocation		**×**					
Randomization		**×**					
Interventions							
tDCS + MNS group		**×**	**×**				
tDCS sham + MNS group		**×**	**×**				
tDCS + MNS sham group		**×**	**×**				
Assessments							
Primary outcome							
CRS-R		**×**	**×**	**×**	**×**	**×**	**×**
Secondary outcomes							
fNIRS		**×**	**×**				
EEG		**×**	**×**				
ERPs		**×**	**×**				
GOS-E		**×**			**×**	**×**	
fMRI		**×**					**×**
Adverse Events			**×**	**×**	**×**	**×**	**×**

× Represents data collection timepoint. tDCS, transcranial direct current stimulation; MNS, median nerve stimulation; CRS-R, Coma Recovery Scale-Revised; fNIRS, Functional Near-Infrared Spectroscopy; EEG, Electroencephalography; ERPs, Event-Related Potentials; GOS-E, Glasgow Outcome Scale-Extended; fMRI, Functional magnetic resonance imaging.

#### Follow-up retention strategy

To minimize attrition during the 6-month follow-up period, we will implement several retention strategies: (1) Assigning a dedicated research coordinator to maintain regular contact with participants’ families/caregivers; (2) Providing flexible scheduling options for follow-up assessments, including the possibility of home visits when appropriate; (3) Reimbursing transportation expenses for hospital visits; (4) Implementing telephone or video follow-ups for interim check-ins between scheduled assessments; (5) Providing clear information about the importance of complete follow-up data; (6) Sending reminder communications before each scheduled assessment; and (7) Collecting multiple contact methods (phone, email, alternative contacts) to maintain communication if primary contact methods fail. Additionally, we will monitor reasons for withdrawal and address any systematic issues that emerge during the trial.

### Data collection and study safety

#### Data collection and quality control

This study will utilize an advanced electronic data capture (EDC) system for data management, employing the REDCap (Research Electronic Data Capture) platform (37). This system features real-time data validation, audit trails, and automated logic checks, significantly reducing data entry errors. All research personnel will receive specialized training on the REDCap system to ensure accuracy and consistency in data collection.

#### Study safety

Based on previous research, transcranial direct current stimulation and median nerve stimulation are considered relatively safe, non-invasive techniques (16). However, we will closely monitor potential adverse events, including but not limited to: (1) mild discomfort, redness, or itching at the stimulation site; (2) transient headache or dizziness; (3) nausea; (4) fatigue. To address these potential adverse events, we have developed a detailed response plan: (1) All research personnel will receive training in adverse event identification and management. (2) Given that patients with prolonged disorders of consciousness (pDoC) cannot reliably self-report subjective adverse events, a comprehensive monitoring approach has been implemented, including systematic observation of objective signs (skin reactions, autonomic changes such as heart rate, blood pressure, and sweating, facial expressions, and behavioral responses); physiological parameter monitoring (temperature, blood pressure, and heart rate before and after each session); neurophysiological indicators (EEG changes during treatment and follow-up that may indicate discomfort or adverse responses); caregiver reports (detailed inquiries to family members and caregivers about any unusual behaviors or responses); and clinical judgment (comprehensive assessment by experienced clinicians familiar with detecting subtle signs of discomfort in non-communicative patients). (3) Detailed assessments using the above methods will be conducted before and after each treatment session and at all follow-up visits. (4) Any identified adverse events will be documented and evaluated by a physician not involved in the direct treatment delivery. (5) For adverse events management, we will implement a standardized classification system based on the Common Terminology Criteria for Adverse Events (CTCAE v5.0). All adverse events will be graded on a 5-point scale (1: mild; 2: moderate; 3: severe; 4: life-threatening; 5: death-related) and systematically documented in a dedicated adverse event log. Events of grade 3 or higher will be reported to the ethics committee within 24 h.

Treatment will be immediately discontinued if any of the following criteria are met: (1) Grade 3 or higher adverse events related to the intervention; (2) Recurring grade 2 adverse events that persist despite mitigation measures; (3) Participant or legal representative request; (4) Investigator judgment that continuation poses unacceptable risk. The decision to discontinue treatment will be made by a physician not directly involved in intervention delivery, and all discontinuations will be reported to the ethics committee and study safety monitoring board within 48 h.

### Statistical analysis

#### Analysis principles

This study will employ intention-to-treat (ITT) analysis as the primary analytical approach to evaluate the efficacy of transcranial direct current stimulation combined with median nerve stimulation in patients with chronic disorders of consciousness (38). The ITT analysis will include all randomized patients, regardless of protocol adherence or treatment completion. Additionally, we will conduct a per-protocol (PP) analysis as a supplementary measure to assess treatment effects in patients who fully adhered to the study protocol (39).

#### Statistical methods

(1) Descriptive statistics: Continuous variables will be presented as mean ± standard deviation (for normally distributed data) or median and interquartile range (for non-normally distributed data); categorical variables will be presented as frequencies and percentages.

(2) Between-group comparisons: Baseline characteristics: Continuous variables will be compared using one-way analysis of variance (ANOVA) (for normally distributed data) or Kruskal-Wallis test (for non-normally distributed data); categorical variables will be compared using chi-square test or Fisher’s exact test.

(3) Primary outcome analysis: First, within-group comparisons will be conducted to assess changes in CRS-R scores from baseline to each follow-up time point within each intervention group. Paired t-tests (for normally distributed data) or Wilcoxon signed-rank tests (for non-normally distributed data) will be used for these comparisons. This will provide insights into the therapeutic effectiveness of each intervention approach. Subsequently, between-group comparisons will be performed using a 3 × 6 mixed repeated measures analysis of covariance (ANCOVA) with group (tDCS+MNS, sham tDCS+MNS, and tDCS+sham MNS) as a between-subjects factor and time (baseline, 4 weeks post-treatment, and follow-ups at 2 weeks, 4 weeks, 12 weeks, and 24 weeks) as a within-subjects factor. To control for potential confounding variables, baseline age, sex, duration of consciousness disorder, and baseline severity will be included as covariates if significant differences are observed at baseline despite randomization. Post-hoc analyses with appropriate multiple comparison corrections will be used to identify specific group differences at each time point. The analysis will include all assessment time points (baseline, 4 weeks post-treatment, and follow-ups at 2 weeks, 4 weeks, 12 weeks, and 24 weeks) (40). If data violate normality assumptions, generalized estimating equations (GEE) models will be employed (41).

(4) Secondary outcome analyses: For continuous secondary outcomes (e.g., fNIRS, EEG, and ERP metrics), both within-group and between-group analyses will be conducted following the same approach as the primary outcome. Within-group changes will be assessed first, followed by between-group comparisons with appropriate covariate adjustments. Categorical secondary outcomes (e.g., GOS-E) will be analyzed using ordinal logistic regression, with baseline measurements included as covariates to account for potential confounding.

(5) Missing data handling: Multiple imputation techniques will be used to handle missing data, reducing bias and improving statistical power, The imputation model will include all primary and secondary outcomes, as well as key baseline covariates (age, sex, time since injury, baseline CRS-R score, and consciousness state). We will generate 20 imputed datasets, as recommended by methodological guidelines (42); Results will be pooled using Rubin’s rules, and sensitivity analyses will include complete case analysis to assess the impact of missing data on results.

(6) Subgroup analyses: Pre-specified subgroup analyses will be conducted based on age, sex, duration of consciousness disorder, and baseline CRS-R scores to explore potential effect modifiers. To control for multiple comparisons in these subgroup analyses, we will apply the same Bonferroni correction approach used for secondary outcomes. Furthermore, we will clearly label these analyses as exploratory and interpret the results with appropriate caution regarding potential Type I error inflation.

(7) Sensitivity analyses: In addition to ITT analysis, PP analysis will be performed to evaluate treatment effects in patients who fully adhered to the protocol.

(8) Covariate handling: Despite our stratified randomization strategy, potential imbalances in baseline characteristics might still exist. Therefore, we will compare baseline demographic and clinical characteristics between groups. If any significant differences are detected (*p* < 0.05), these variables will be treated as covariates in subsequent analyses to minimize confounding. Additionally, baseline measurements of outcome variables will routinely be included as covariates in the respective analyses to account for potential regression to the mean effects and to increase statistical power.

All statistical analyses will be conducted using R software (version 4.1.0 or higher), with a significance level set at *α* = 0.05 (two-sided). To control for Type I error inflation due to multiple comparisons, Bonferroni correction will be applied to adjust *p*-values for secondary outcomes (43).

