## Study design

This is a prospective, single-center, three-arm parallel randomized controlled trial. Patients will be randomly assigned to three groups: (1) tDCS+MNS group: receiving real tDCS and MNS treatment; (2) Sham tDCS+MNS group: receiving sham tDCS and real MNS treatment; (3) tDCS+Sham MNS group: receiving real tDCS and sham MNS. Each group will consist of 27 patients, with treatment lasting for 4 weeks (22).

Randomization will be implemented using a web-based central randomization system, developed by an independent statistician using the “blockrand” package in R software (version 4.1.0) (23). We will employ a stratified randomization strategy to ensure balanced baseline characteristics across groups. Randomization will be stratified by age (≤50 years/>50 years) and baseline consciousness level (vegetative state/minimally conscious state) (9). The allocation ratio will be 1:1:1, using variable block sizes (4 or 6) to enhance allocation unpredictability. To ensure allocation concealment, the randomization sequence will be stored in the central randomization system, and the study coordinator will only obtain the allocation result through this system after the patient has completed all baseline assessments and confirmed eligibility. The system will send the allocation result to the therapist responsible for implementing the intervention via encrypted email.

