## Discussion

pDoC following ICH severely impact patients’ quality of life and impose a significant societal burden (5). Despite some efficacy shown by existing treatments, notable limitations persist (10). In recent years, the combined application of tDCS and MNS has garnered attention due to its safety, ease of operation, and relatively low cost. Preliminary studies suggest potential benefits for patients with disorders of consciousness, but existing research has primarily focused on traumatic brain injury patients, with small sample sizes and short follow-up periods. Recent evidence indicates that 3–12 months post-ICH may be a critical period for neurological recovery, yet systematic studies targeting pDoC patients during this period are lacking. Given these research gaps and urgent clinical needs, we designed this prospective randomized controlled trial to investigate the therapeutic effects of tDCS combined with MNS in pDoC patients 3–12 months post-ICH. This study will conduct a 6-month follow-up, comprehensively assessing the long-term efficacy, safety, and potential mechanisms of this combined intervention. Through this research, we aim to provide more reliable and comprehensive scientific evidence for the clinical management of ICH-induced pDoC, paving the way for improving patient prognosis and quality of life.

Our study design has several notable advantages. Firstly, we focus on pDoC patients 3–12 months post-ICH, a period considered critical for neurological recovery. By targeting this specific population, we aim to obtain more precise and valuable data on treatment efficacy. Secondly, we employ a combined application of tDCS and MNS, a combination that may enhance therapeutic effects through synergistic action (46). tDCS modulates cortical excitability, while MNS stimulates the peripheral nervous system, potentially promoting more comprehensive neural network reorganization (47, 48). Thirdly, our 6-month long-term follow-up design will help evaluate sustained treatment effects and potential long-term safety issues. Lastly, we adopt multidimensional assessment metrics, including behavioral, electrophysiological, and neuroimaging indicators. This comprehensive assessment approach not only provides stronger evidence of therapeutic efficacy but may also reveal biomarkers of consciousness recovery in pDoC patients (49). This multifaceted evaluation strategy helps us better understand treatment effects and their underlying neural mechanisms.

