Despite the numerous advantages of our study design, some limitations exist. Firstly, our study focuses only on pDoC patients following ICH, which may limit the applicability of our findings to pDoC patients with other etiologies. Secondly, although we implement a 6-month follow-up period, it may still be insufficient to comprehensively evaluate long-term treatment effects. Thirdly, while we adopt multidimensional assessment metrics, certain potential neurobiological changes may not be fully captured by existing technologies. Additionally, due to ethical considerations, we cannot implement a placebo control, which may affect the precise evaluation of treatment efficacy. Lastly, as a single-center study, we also recognize inherent limitations to the generalizability of our findings. Regional variations in standard care practices, rehabilitation protocols, and population demographics may influence treatment outcomes. Future multi-center trials across diverse geographical regions would be valuable to validate our findings and strengthen the evidence base for this intervention approach. Despite these limitations, we believe this study will provide valuable insights and data for the treatment of pDoC patients.

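### Before-after tests within each arm open the primary analysis as evidence of effectiveness, but a within-arm change cannot be attributed to stimulation in this design

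*Protocol article*

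**What the plan says.** The protocol article, Statistical methods, item (3), sets the order of the primary outcome analysis. It begins: "First, within-group comparisons will be conducted to assess changes in CRS-R scores from baseline to each follow-up time point within each intervention group". The tests are named: "Paired t-tests (for normally distributed data) or Wilcoxon signed-rank tests (for non-normally distributed data) will be used for these comparisons". Their purpose is then given: "This will provide insights into the therapeutic effectiveness of each intervention approach". Only after this comes the comparison between groups, a 3 × 6 mixed repeated measures ANCOVA with corrected post-hoc contrasts at each time point.

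Item (4) carries the same order over to continuous secondary outcomes: "Within-group changes will be assessed first, followed by between-group comparisons with appropriate covariate adjustments".

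The Study design section lists three arms: both stimulations real, only MNS real, only tDCS real. None is sham for both. The limitations paragraph of the Discussion accepts this: "due to ethical considerations, we cannot implement a placebo control". On the enrolment window the Discussion says: "Recent evidence indicates that 3–12 months post-ICH may be a critical period for neurological recovery".

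**The concern.** A change from baseline within one arm is the sum of whatever happened to those patients: any effect of stimulation, recovery that would have come anyway, the rehabilitation that all arms receive, and regression to the mean (which item (8) of Statistical methods itself mentions). A paired test asks whether that sum is zero. It cannot say which part is due to stimulation. That would need an arm without stimulation, and there is none.

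The protocol nevertheless places these tests first under the primary outcome and ties them to the effectiveness of each intervention. At stake is a report that one or more treatments work, on evidence that would look the same if stimulation did nothing. The number of tests adds to this, because no multiplicity control is stated for them. Bonferroni is stated for secondary outcomes and subgroups, and the unspecified post-hoc correction is for group differences.

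**Working it through.** **Inputs from the protocol.** SD 7.3 CRS-R points, correlation among repeated measures 0.5, and 22 patients per arm raised to 27 for dropout (Sample size); two-sided α = 0.05 (Statistical methods); five post-baseline CRS-R visits at weeks 4, 6, 8, 16 and 28 (Table 1). The abstract also gives a total of 138, which does not match three groups of 27; I use 27 per arm.

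**Assumptions.** The protocol gives no figure for change without stimulation. I assume the same gain in all three arms and no stimulation effect, and show 0, 2 and 3 points. A correlation of 0.7 is tried beside the protocol's 0.5. The SD of 7.3 is taken as the SD of a single score.

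**The plan's own figure.** The protocol gives no error rate for the within-arm tests, so there is none to reproduce. The 22 per arm does reproduce for the group × time interaction if λ = f²·N·(m−1)·ε with f = 0.25, m = 6, ε = 0.75 (power 0.81 at N = 66), a convention in which the stated correlation plays no part. Then 22 × 1.2 = 26.4, rounded up to 27. This point does not depend on that calculation.

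**Step 1. Number of tests.** 3 arms × 5 visits = 15.

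**Step 2. SD of change.** SD × √(2(1 − ρ)):
- ρ = 0.5: 7.3 × √1.0 = 7.30
- ρ = 0.7: 7.3 × √0.6 = 5.65

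**Step 3. One paired t-test, 27 per arm.** Noncentrality = gain ÷ (SD of change ÷ √27); critical value t(26) = 2.056; probability from the noncentral t distribution.

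| Shared gain | ρ | Noncentrality | Chance of p < 0.05 with no stimulation effect |
|---|---|---|---|
| 0 | any | 0 | 0.050 |
| 2 | 0.5 | 2 ÷ 1.405 = 1.42 | 0.278 |
| 2 | 0.7 | 2 ÷ 1.088 = 1.84 | 0.425 |
| 3 | 0.5 | 3 ÷ 1.405 = 2.14 | 0.538 |
| 3 | 0.7 | 3 ÷ 1.088 = 2.76 | 0.756 |

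With 22 per arm and ρ = 0.5 the figures are 0.232 at 2 points and 0.452 at 3.

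**Step 4. At least one of 15 significant when nothing changes.** If the tests were independent: 1 − 0.95¹⁵ = 0.54. They are not, because the five tests in an arm share the baseline and the patients. Simulation of 20,000 trials per setting, with 22 or 27 per arm and ρ = 0.5 or 0.7, gives about 46%.

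**Step 5. The between-group test on the same data.** A gain common to all arms cancels in a difference between arms. In the same simulations a three-arm comparison of week-4 change is significant in about 5% of trials at every shared gain tried.

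**The case against.** The strongest reply is that the text claims little. It speaks of insights, sets no decision rule on the within-arm tests and does not make the ANCOVA depend on them. The randomised comparison follows with corrected post-hoc contrasts, Bonferroni is stated for secondary outcomes, and the Discussion admits the lack of a placebo control. All of that stands, and it limits the point to the within-arm tests and the sentence that interprets them. It does not rescue that sentence: the insight claimed is therapeutic effectiveness, within the primary analysis, and the admission in the Discussion is not carried back to it. The subgroup analyses are labelled exploratory; these tests are not.

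A second reply is that entry requires a stable CRS-R and the population is described as chronic. This lessens natural change but does not exclude it: the rule tolerates up to 2 points over a minimum of 2 weeks, and observation then runs to week 28. It is also fair that the protocol does not itself forecast spontaneous recovery. The Introduction uses the critical window to argue for responsiveness to neuromodulation. Unaided recovery is a reasonable inference, and its size is unknown.

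A reader might infer more than the documents support:
- **That all three arms would probably look effective when stimulation does nothing.** At week 4 with 27 per arm, all three are significant in only 2% to 8% of trials at 2 points (0.278³ to 0.425³) and 15% to 43% at 3 points. It becomes likely (65% to 90%) only at 3 points and counting any visit.
- **That superiority will be claimed from one arm being significant and another not.** The protocol nowhere proposes this; it plans direct contrasts between groups.
- **That the 46% is the trial's false-positive rate.** It is not, because the protocol does not make success depend on any of the 15 tests.

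**Conclusion.** The concern holds in a limited form. Reading within-arm before-after tests as effectiveness of each intervention is invalid here, whatever the size of natural change, because no arm shows what happens without stimulation. How often it would mislead depends on assumptions: 5% per test with no shared change, 28% to 42% at 2 points and 54% to 76% at 3 points (equal gain in all arms, 27 per arm, SD 7.3, correlation 0.5 to 0.7). The 46% for at least one of 15 needs no assumed gain, only no change and the protocol's stated variance structure or one close to it.

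The between-group analysis is untouched by this point. It can estimate what tDCS adds to MNS and what MNS adds to tDCS; it cannot estimate either stimulation alone. This should be corrected, but it does not undermine the trial.

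**What to change.** In Statistical methods, item (3), delete the sentence on therapeutic effectiveness. In items (3) and (4), report within-arm changes as means with confidence intervals, labelled descriptive, for primary and continuous secondary outcomes. State that efficacy conclusions rest solely on the two randomised contrasts: the combination against sham tDCS + MNS (tDCS added to MNS), and the combination against tDCS + sham MNS (MNS added to tDCS). Add that the effect of either stimulation alone cannot be estimated in this design, so that the analysis section agrees with the limitation already admitted in the Discussion.

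The cost is a wording change in the protocol and analysis plan and fewer p-values to report. It needs no extra patients, visits or measurements.

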### Outcome measures

#### Primary outcome measure

The primary outcome measure is the change in total score on the Coma Recovery Scale-Revised (CRS-R) from baseline to post-treatment (24). The CRS-R is the gold standard for assessing patients with disorders of consciousness and comprises six subscales: auditory, visual, motor, oromotor, communication, and arousal, with a total score range of 0–23 (32). CRS-R assessments will be conducted by trained evaluators at baseline, after 4 weeks of treatment, and at 2 weeks, 4 weeks, 12 weeks, and 24 weeks post-intervention. To ensure consistency and accuracy, all evaluators will undergo standardized training and pass a video scoring test to ensure inter-rater reliability (ICC > 0.8) (24).

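### The Week-4 CRS-R change is declared primary, but the primary analysis is a three-group, six-visit model with no deciding effect and no planned comparison of the combination with each component

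*Protocol article*

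**What the plan says.** Primary outcome measure: "The primary outcome measure is the change in total score on the Coma Recovery Scale-Revised (CRS-R) from baseline to post-treatment". The visit schedule fixes the timing: "post-treatment (Week 4), and follow-up (Weeks 6, 8, 16, and 28". The declared change therefore ends at Week 4.

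Statistical methods, item (3), makes the between-group analysis a "3 × 6 mixed repeated measures analysis of covariance (ANCOVA) with group" as the between-subjects factor and "time (baseline, 4 weeks post-treatment, and follow-ups at 2 weeks, 4 weeks, 12 weeks, and 24 weeks) as a within-subjects factor". Time-specific comparisons follow: "Post-hoc analyses with appropriate multiple comparison corrections will be used to identify specific group differences at each time point". The only correction named anywhere is Bonferroni, and it is assigned to secondary outcomes and subgroups.

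There are two rules for baseline. Item (3) says that "baseline severity will be included as covariates if significant differences are observed at baseline despite randomization". Item (8) says that "baseline measurements of outcome variables will routinely be included as covariates in the respective analyses". Item (3) also contains a switch of model: "If data violate normality assumptions, generalized estimating equations (GEE) models will be employed".

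**The concern.** The trial compares a combination with each of its two components. Its declared outcome therefore calls for two differences at Week 4: tDCS+MNS against sham tDCS+MNS, and tDCS+MNS against tDCS+sham MNS. The stated primary model gives a group effect, a time effect and a group-by-time interaction over Weeks 0 to 28, and none is named as decisive. The group effect and the interaction are non-directional across three arms. Either can be significant because of a late divergence, because one component beats the other, or because the combination is worse.

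The trial could then report a significant primary analysis while the declared Week-4 comparison is null. The choice among effects, visits and pairs would be made after the data are seen. Baseline is also both one of the six response levels and a covariate, under two rules that disagree about when it enters.

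**Working it through.** **Does the sample size reveal the deciding effect?** The article gives 22 per group (N = 66) for the 3 × 6 model, with f = 0.25, m = 6 visits, ρ = 0.5, ε = 0.75, α = 0.05 and 80% power.

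- Interaction: λ = f²·N·m·ε/(1−ρ) = 0.0625 × 66 × 6 × 0.75/0.5 = 37.1. Power is 0.998, and 10 per group would suffice.
- Group effect: λ = f²·N·m/(1+(m−1)ρ) = 0.0625 × 66 × 6/3.5 = 7.07. Power is 0.64, and 31 per group would be needed.

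Neither gives 22. The closest route found is an alternative effect-size option (23 per group), which does not use the stated ρ. So this section does not show which effect was meant. Whether 22 is correct is a separate matter.

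**Number of post-hoc tests.** 3 pairs × 5 post-baseline visits = 15, of which 2 answer the declared question.

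**What a significant result would mean.** Simulation inputs: SD 7.3 and a 4-point difference (Sample size section), ρ = 0.5 (same section) with 0.7 as a range, and 22 or 27 per arm. Assumptions: 7.3 is the SD at each visit, and correlation is compound symmetric. There were 4,000 runs per setting at ρ = 0.5 and 2,000 at ρ = 0.7. Cells give the percentage of significant trials at 22 per arm (ρ 0.5) / 27 (ρ 0.5) / 27 (ρ 0.7). The last column is a Week-4 ANCOVA in which the combination must beat both controls, each at two-sided 0.05.

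| True pattern | Group-by-time | Group effect, baseline-adjusted | Week 4, both contrasts |
|---|---|---|---|
| No difference | 4 / 5 / 5 | 5 / 5 / 6 | 0.4 / 0.5 / 0.5 |
| Combination +4 at Weeks 16 and 28 only | 59 / 72 / 94 | 22 / 26 / 32 | 0.4 / 0.5 / 0.6 |
| Combination = tDCS alone, both +4 over MNS alone | 36 / 46 / 74 | 89 / 94 / 98 | 2.6 / 2.5 / 2.4 |
| Combination 4 worse than both | 36 / 46 / 76 | 87 / 94 / 98 | 0 / 0 / 0 |
| Combination +4, sustained | 38 / 46 / 75 | 88 / 94 / 98 | 37 / 47 / 68 |
| Combination +4 at Week 4 only | 37 / 46 / 73 | 9 / 10 / 11 | 38 / 47 / 67 |

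The group-by-time figures are without the covariate; adjusting for baseline raises them by at most 5 points in these rows. Repeat runs agree within a few points, hence the rounded ranges of 60–95% (late only) and 40–75% (tie with tDCS).

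The group-by-time test is about as often significant when the combination ties with tDCS, or is worse than both, as when it is truly better. The two omnibus tests also disagree sharply for late-only and Week-4-only effects. Under a full null, accepting either the unadjusted group effect or the interaction gives 8.5 / 9.5 / 10.0%, so leaving the deciding effect open has a cost.

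**Baseline used twice.** Let y0 be baseline and P the mean of the five later visits. The six-visit mean is (y0 + 5P)/6. Given y0, both the group coefficient and the residual are 5/6 of those for P. A 4-point effect appears as 4 × 5/6 = 3.3, and the F test is unchanged. In the simulation, rejection rates were identical with six levels and with the five post-baseline levels.

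**The case against.** **The plan does analyse Week 4.** A reader might infer that it is never tested. That is not supported: pairwise differences at each time point are specified with a correction. They are post hoc, and the correction is unnamed.

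**Late effects are within the trial's aims.** The Introduction names long-term efficacy, the Abstract gives no time point for the primary outcome, and CRS-R is called primary at every visit. A late effect is thus not irrelevant. It is simply not the declared baseline-to-post-treatment change, so the fault is a primary time point that the analysis does not fix.

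**The omnibus test is valid.** It would be wrong to read the 40–75% as error rates. A three-arm test should reject when arms differ, and each test holds about 5% under a full null. A false claim for the combination arises only if the pairwise follow-up is ignored. This stands. What remains is that no such comparison is declared primary.

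**Power.** One might argue that the six-visit model is less powerful. It is not. The both-contrasts rule has no material advantage over the group-by-time test and is well below the baseline-adjusted group effect (about 88–98% for a sustained 4 points), which answers a different question.

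**Baseline.** The double use neither inflates error nor loses power in the group test, and visit-specific estimates are not diluted.

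**GEE.** A reader might conclude that the fallback cannot hold 5%. Simulated error of about 14–19% applies to an uncorrected 10-df robust Wald test. A single Week-4 contrast under the same estimator gave 6.8%. The article names no variance estimator, which may properly sit in an analysis plan, and the analysts are blinded to group. This is a minor remark.

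**Condensed article.** An article may leave detail to a fuller document. Here, though, it states both a primary outcome and a primary analysis, and the two do not match.

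**Conclusion.** The point holds in this form: the plan does not make its declared primary outcome the primary test. The deciding effect and the combination-versus-component contrasts are not fixed, so a significant primary analysis would not establish that the combination beats its components at Week 4. The Week-4 both-contrasts rule succeeds in about 0.5% of trials with a late-only effect and 2–3% when the combination ties with tDCS.

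These rates rest on the effect patterns shown, on compound symmetry and on reading 7.3 as the SD at each visit; the Sample size section does not say whether it refers to scores or changes. The mismatch between outcome and analysis, and the conflict between items (3) and (8) on baseline, do not depend on any of these.

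**What to change.** - Make the primary test the Week-4 CRS-R difference, from an ANCOVA or from a mixed model on the five post-baseline visits. Always adjust for baseline CRS-R as a covariate and remove it as a response level. Bring items (3) and (8) into line.
- Plan two contrasts: tDCS+MNS versus sham tDCS+MNS, and tDCS+MNS versus tDCS+sham MNS. Claim superiority over both components only if both are significant at two-sided 0.05. Because both are required, alpha need not be split.
- Make later visits secondary.
- Keep this model whatever a normality check shows, with a rank or permutation analysis as sensitivity. If GEE is kept, specify a small-sample-corrected variance.

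The change is to wording only, but it exposes limited power. For 4 points, requiring both contrasts gives about 36–56% at 22 per arm and 44–69% at 27. With ρ = 0.5 the ANCOVA residual SD is 7.3 × √(1 − 0.25) = 6.32, and even a single contrast needs 40 per arm for 80% power. The sponsor should weigh this when confirming the sample size.
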